## Abstract

**Background:**

Venous leg ulcers (VLUs) and VLUs associated with peripheral arterial disease (PAD) are common, recurrent, and costly to manage. Adjunctive biophysical therapies may improve healing outcomes when combined with standard of care (SOC). Concurrent optical and magnetic stimulation (COMS) has shown promising mechanistic and preliminary clinical results but there is a lack of robust randomized controlled trials (RCTs).

**Method:**

This novel adjunct using concurrent optical and magnetic stimulation in a multicenter RCT in Europe (NAZARÉ) is a phase IV, post-market, multicenter, parallel-group, superiority randomized controlled trial conducted in Switzerland, France, Germany, and Austria. A total of 122 adults with VLU or mixed leg ulcers (ankle-brachial index > 0.5 and < 1.30 or ankle artery pressure > 60 mmHg), ulcer area 2–50 cm^2^, and ulcer duration > 30 days and < 2 years will be enrolled. Following a 2-week run-in to confirm < 30% area reduction under SOC, participants will be randomized 1:1 to SOC + COMS or SOC alone. The primary outcome is percentage wound area reduction (PWAR) at week 12, assessed by blinded evaluators using standardized digital planimetry. Secondary outcomes include complete closure, time-to-healing, pain, health-related quality of life, recurrence, and healthcare resource use. Missing outcome data will primarily be analyzed as observed and may be addressed using multiple imputation under the assumption of data being missing at random.

**Discussion:**

This trial will rigorously assess the effectiveness of COMS as an adjunct to standard care for venous and mixed leg ulcers. By targeting chronic wounds and using a pragmatic, multicenter design, it aims to generate robust, generalizable evidence. If effective, COMS could offer a non-invasive, accessible option to enhance healing outcomes and reduce the burden of chronic leg ulcers.

**Trial registration number:**

ClinicalTrials.gov NCT06528873. Registred on 26 July 2024, https://register.clinicaltrials.gov/prs/app/action/SelectProtocol?selectaction=Edit&sid=S000ERKB&uid=U0003LG4.

## Administrative information

Note: The numbers in curly brackets in this protocol refer to SPIRIT checklist.

**Table Taba:** 

Title (1)	Adjunctive Optical and Magnetic Stimulation for Venous and Mixed Etiology Leg Ulcers: Protocol for the NAZARÉ Multicenter Randomized Controlled Trial
Trial registration	ClinicalTrials.gov: NCT06528873
Protocol version	Protocol version 1, version 13.10.2025
Funding	This study is funded by an unrestricted grant from Piomic Medical AG, Zurich, Switzerland.

## Introduction

### Background and rationale

Chronic leg ulcers (LU), particularly venous leg ulcers (VLUs), represent one of the most prevalent and persistent forms of lower extremity ulceration [1], with substantial impacts on patients’ physical health, quality of life, and economic well-being [2, 3]. VLUs account for up to 80% of all lower extremity ulcers and remain a leading cause of chronic wound care needs worldwide [4]. The global pooled point prevalence in the general population is estimated at 0.32% (95% CI, 0.11–0.60), and the annual incidence at 0.17% (95% CI, 0.08–0.29) [5]. Prevalence increases markedly with age, with older adults, particularly those aged ≥ 65 years, disproportionately affected. Recurrence is frequent, with up to 76% of patients experiencing ulcer recurrence within one year of healing, underscoring the chronic and relapsing nature of the condition [6].

The epidemiology of VLUs varies across regions, reflecting differences in population demographics, comorbidity profiles, and health system structures. High-income countries report prevalence rates between 0.1% and 0.6% in the general population, with rates exceeding 2% among individuals over 80 years of age [7]. Risk factors for recurrence include persistent venous reflux, inadequate compression maintenance, obesity, reduced mobility, and poor adherence to treatment regimens [3, 8]. Peripheral arterial disease (PAD) further complicates ulcer healing by reducing arterial inflow, leading to a mixed etiology ulcer with poorer prognoses and fewer effective treatment options [7].

The clinical and economic burden of VLUs is considerable, with estimated annual direct medical costs of approximately $10.73 billion (USD) across the studied geographies, averaging about $5,527 per patient per year for those managed conservatively [9]. In the UK, chronic wounds account for approximately 4% of total National Health Service spending, with VLUs representing one of the most resource-intensive categories [10]. Similar patterns are reported in the USA and Australia [11, 12]. Direct costs include dressings, compression systems, nursing visits, and hospital admissions, while indirect costs, such as work absenteeism, informal caregiving, and early retirement, add substantially to the societal impact [13].

Pathophysiologically, VLUs are driven by sustained venous hypertension, which leads among others to leukocyte activation, inflammatory mediator release, and microcirculatory dysfunction [1]. These processes impair the delivery of oxygen and nutrients essential for tissue repair [1]. In cases of VLU and PAD, impaired arterial perfusion exacerbates tissue hypoxia, further delaying healing [14]. Standard of care (SOC) for VLUs centers on compression therapy, wound bed preparation, infection control, and management of systemic comorbidities [12]. Compression therapy remains the gold standard of conservative treatment. However, its effectiveness is limited by inconsistent patient adherence, which is often hindered by discomfort, difficulty with application, and insufficient patient education [15–17].

Given these challenges, there is increasing interest in adjunctive therapies that target underlying pathophysiological mechanisms. Concurrent optical and magnetic stimulation (COMS) is a novel biophysical approach that integrates photobiomodulation in the red (630–680 nm) and near-infrared (800–860 nm) spectrum with low-intensity pulsed magnetic stimulation (1–100 mT). Photobiomodulation enhances mitochondrial oxidative metabolism via cytochrome c oxidase activation, increases adenosine triphosphate (ATP) production, and modulates inflammation through nitric oxide photodissociation. Low-intensity magnetic stimulation influences mechanosensitive ion channels, modulates vascular tone, and promotes angiogenesis [18–20].

Preliminary clinical data suggest that COMS may accelerate wound healing, reduce pain, and improve quality of life in patients with chronic wounds [21]. However, these findings are derived primarily from small-scale, uncontrolled studies with limited follow-up, leaving the magnitude and durability of any clinical benefit uncertain. There is a clear need for adequately powered, randomized controlled trials (RCTs) with rigorous methodology to assess the effectiveness of COMS as an adjunct to SOC.

The novel adjunct using concurrent optical and magnetic stimulation for venous leg ulcers in a multicenter randomized trial in Europe (NAZARÉ) has been designed to address this gap by evaluating whether the addition of COMS to SOC results in greater percentage wound area reduction (PWAR) at 12 weeks compared with SOC alone. Secondary objectives include assessing complete wound closure rates, time-to-healing, pain, health-related quality of life, recurrence rates, and healthcare resource utilization over a 24-week period. This trial is expected to provide robust, clinically relevant evidence that will inform clinical practice and healthcare policy in the management of VLUs and VLU + PAD.

### Objectives

The primary objective of the NAZARÉ trial is to determine whether SOC plus COMS achieves greater percentage wound area reduction (PWAR) at 12 weeks compared with SOC alone. Secondary objectives are to assess PWAR and complete wound closure at each visit, time-to-healing, pain, health-related quality of life, recurrence, and healthcare resource use over a 24-week period.

### Trial design

The NAZARÉ trial is a phase IV, post-market, multicenter, parallel-group, superiority, RCT with blinded outcome assessment conducted across European specialist wound care centers. It is designed to evaluate the efficacy of COMS when used as an adjunct to standard of care (SOC) in adults with VLUs or VLUs complicated by PAD.

## Methods: participants, interventions, and outcomes

### Study setting

The trial will be conducted at ten specialist wound care centers across Switzerland, France, Germany, and Austria. All participating sites have prior Good Clinical Practice (GCP)-compliant experience with interventional wound trials and will follow harmonized SOC protocols to minimize inter-site variability.

### Eligibility criteria

Inclusion criteria require that participants are aged 18 years or older, have a clinical diagnosis of VLU or VLU + PAD, and present with an ankle-brachial index (ABI) between 0.5 and 1.3 or an ankle artery pressure above 60 mmHg. Eligible ulcers must measure between 2 and 50 cm^2^ after debridement at screening and have been present for more than 30 days but less than 2 years. For patients with diabetes, the glycated hemoglobin (HbA1c) must be ≤ 12% at screening. All participants must provide written informed consent prior to any trial-specific procedure.

Exclusion criteria include pregnancy or lactation, active malignancy within the ulcer region, use of photosensitizing medication within the past 30 days, severe immunosuppression (including chronic corticosteroid therapy at > 10 mg/day prednisolone equivalent), New York Heart Association (NYHA) class III or IV heart failure, end-stage renal disease requiring dialysis, ulcer area reduction greater than 30% during the run-in phase, active infection requiring systemic antibiotics at baseline, use of advanced wound therapies (e.g., negative pressure wound therapy, skin substitutes, or hyperbaric oxygen therapy) within 2 weeks before screening, or participation in another interventional clinical trial within the past 30 days.

Eligibility criteria for study staff: Only investigators with experience in wound management and trained in COMS device use perform the intervention.

### Who will take informed consent?

Informed consent will be obtained by the site’s principal investigator or a study nurse who is GCP-certified. Potential participants will receive both verbal and written information about the study purpose, procedures, potential risks, benefits, and data confidentiality. Adequate time will be provided for questions before signing the consent form.

### Additional consent provisions for collection and use of participant data

If additional photographic data are collected for ancillary analyses or educational purposes, separate consent will be obtained specifying their scope, duration of storage, and anonymization procedures. Participants may opt out of future use without affecting trial participation.

### Explanation for choice of comparators

The comparator (SOC alone) reflects best practice for VLU management per international guidelines [22]. Its inclusion allows the effect of COMS to be isolated and compared against standard evidence-based wound care.

## Interventions

### Run-in phase

A 2-week run-in period precedes randomization (see Fig. 1). During this phase, all participants receive optimized SOC, including wound cleansing, appropriate dressings, debridement when indicated, and compression therapy according to international guidelines. Wound area measurements are taken at screening and at the end of the run-in period. Participants whose ulcer area decreases by more than 30% during this period are excluded from randomization, as such wounds are likely to heal adequately with SOC alone. This strategy enriches the trial population with chronic ulcers and increases the study’s power to detect a true treatment effect.

**Fig. 1 Fig1:**
[figure not shown]
NAZARÉ study timeline with phases and endpoints schedule

### Standard of care (SOC)

SOC will be delivered in accordance with evidence-based guidelines [12, 23] and will be standardized across sites. This includes the use of multicomponent compression therapy to achieve an ankle pressure of 40–60 mmHg during the decongestion phase, followed by maintenance therapy with class II or III compression stockings. Wound care will focus on maintaining a moist wound environment, regular debridement, infection control, and optimization of systemic conditions such as glycemic control, blood pressure, and lipid profile.

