### Visit schedule

Participants attend visits at screening (week −2), baseline/randomization (week 0), and follow-ups at weeks 2, 4, 6, 8, 10, 12, 16, 20, and 24. Each visit includes ulcer assessment, wound photography, compression therapy documentation, changes in concomitant medications/therapies documentation, economic parameters documentation, and adverse event monitoring. Health-related quality of life and pain (Visual Analog Scale (VAS)) are assessed at baseline (week 0) and after 3 months (week 12). The 24-week visit assesses longer-term healing outcomes and ulcer recurrence.

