## Discussion

This study is designed to rigorously assess the efficacy of COMS as an adjunct to SOC in venous and mixed-etiology leg ulcers. These conditions represent a substantial and persistent challenge in wound management, with high prevalence, prolonged healing times, and frequent recurrences, all of which translate into a significant personal and societal burden [3]. Even with optimal SOC, including compression therapy, a substantial proportion of ulcers remain unhealed for extended periods, and recurrence is common within months of closure [28, 29].

One of the distinctive features of the NAZARÉ trial is the incorporation of a 2-week run-in phase prior to randomization. This methodological choice is based on evidence that early healing trajectories can predict eventual outcomes, and that wounds demonstrating rapid healing under SOC alone are less likely to benefit from additional interventions. By excluding ulcers that reduce in size by more than 30% during the run-in period, the study enriches its population for chronic ulcers, thereby improving statistical efficiency and increasing the likelihood of detecting a true treatment effect. This design also reduces heterogeneity in the study population, which is especially important in multicenter, international trials.

The pragmatic elements of the trial, such as allowing SOC to be delivered within harmonized but flexible guidelines and conducting the study in diverse clinical settings, enhance external validity. This approach ensures that the results, if positive, are generalizable to real-world practice across healthcare systems with varying resources and workflows. However, pragmatism also comes with trade-offs, including the inability to fully standardize all aspects of care and the potential for performance bias due to the absence of blinding among patients and treating clinicians.

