If COMS demonstrates efficacy, it could be integrated into outpatient and community wound care settings as a non-invasive, well-tolerated adjunct to compression therapy. The portability and relatively short treatment duration make COMS compatible with home-based care, which could further improve accessibility and adherence. Particularly relevant in this context are VLU patients with an arterial component, where PAD limits the safe application of compression to the level that the venous component of the ulcer would otherwise require. For these patients, novel physical therapies may be especially important to compensate for the restricted use of high compression.

Future research could focus on identifying specific patient subgroups, such as those with mixed etiology LUs, recurrent disease, or poor compression adherence, who might derive the greatest benefit. In addition, cost-effectiveness analyses would be essential to inform healthcare policy and reimbursement decisions.

Conversely, if COMS does not demonstrate a clinically relevant benefit, the findings will still provide valuable guidance by redirecting resources towards more promising interventions, refining patient selection criteria, and improving trial designs for advanced wound care technologies. Regardless of the outcome, the NAZARÉ trial will contribute robust, high-quality evidence to an area of wound care where meaningful data are currently largely lacking.

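### The decongestion compression target of 40–60 mmHg carries no arterial condition, so for a narrow group eligible by ABI its upper end can reach ankle arterial pressure

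*Protocol article*

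**What the plan says.** Four parts of the protocol article bear on this.

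- **Standard of care (SOC).** Care follows cited guidelines and is standardized across sites. It includes "multicomponent compression therapy to achieve an ankle pressure of 40–60 mmHg during the decongestion phase", followed by stockings for maintenance. The section does not mention ABI, ankle pressure or PAD.
- **Eligibility criteria.** Patients with a venous ulcer, with or without PAD, qualify with "an ankle-brachial index (ABI) between 0.5 and 1.3 or an ankle artery pressure above 60 mmHg". Either limb of that condition is enough. The Abstract gives the ABI limits as strictly above 0.5 and below 1.30.
- **Run-in phase and Control arm.** From two weeks before randomization "all participants receive optimized SOC", with compression by reference to international guidelines. The control arm's standard care is the same as the experimental arm's.
- **Discussion.** For patients with an arterial component, "PAD limits the safe application of compression to the level that the venous component of the ulcer would otherwise require". New physical therapies are said to matter for them "to compensate for the restricted use of high compression".

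Two further statements qualify the target. Under Study setting, sites "will follow harmonized SOC protocols to minimize inter-site variability". The Discussion describes the design as "allowing SOC to be delivered within harmonized but flexible guidelines".

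**The concern.** The only compression figure in the article is written for the whole trial population, while the Discussion says that part of this population cannot safely receive the compression a venous ulcer would call for. The intervention text does not carry that limit into the target.

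The eligibility rule leaves the gap open. Had an ankle pressure above 60 mmHg been required of everyone, the top of the target would always lie below ankle arterial pressure at entry. Because the two arterial criteria are alternatives, the 60 mmHg floor protects only those who enter by that route.

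At stake is the safety of a few participants with PAD, in either arm. A site working at the top of the printed range could apply external pressure as high as, or higher than, the arterial pressure at the ankle, and would still be following the text.

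**Working it through.** The 40–60 mmHg target is prescribed, not derived, so there is no figure of the plan's to reproduce. The check is whether an eligible participant can have an ankle arterial pressure inside the target range.

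**Inputs**
- Target: 40 to 60 mmHg at the ankle (Standard of care).
- Eligibility: ABI above 0.5, or ankle artery pressure above 60 mmHg (Eligibility criteria; Abstract).
- Brachial systolic pressure: not given in the article. Assumed, and varied from 100 to 160 mmHg.

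**Formula.** By the definition of the index, ankle pressure = ABI × brachial systolic pressure.

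**Step 1: ankle pressure of a participant entering by ABI (mmHg)**

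| Assumed systolic | ABI 0.51 | ABI 0.55 | ABI 0.60 |
|---|---|---|---|
| 100 | 51.0 | 55.0 | 60.0 |
| 110 | 56.1 | 60.5 | 66.0 |
| 120 | 61.2 | 66.0 | 72.0 |
| 140 | 71.4 | 77.0 | 84.0 |
| 160 | 81.6 | 88.0 | 96.0 |

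**Step 2: highest ABI at which 60 mmHg meets or exceeds ankle pressure** (60 ÷ systolic)
- Systolic 100: 60/100 = 0.600
- Systolic 110: 60/110 = 0.545
- Systolic 115: 60/115 = 0.522
- Systolic 120: 60/120 = 0.500, which is not eligible when ABI must exceed 0.5

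The overlap therefore needs a systolic pressure below 120 mmHg and an ABI between 0.5 and 60/systolic. If an ABI of exactly 0.5 were admitted, a systolic of exactly 120 would also touch the limit.

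**Step 3: lower parts of the range.** At ABI 0.51:
- The 50 mmHg midpoint equals ankle pressure at a systolic of 50/0.51 = 98.0.
- The 40 mmHg lower end equals it at 40/0.51 = 78.4.

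So at ordinary blood pressures a site can comply at the lower end and stay below ankle pressure.

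**Step 4: ankle-pressure route.** This needs no assumption. The lowest whole-number eligible value is 61 mmHg, and 61 − 60 = 1 mmHg. The margin is thin, but there is no overlap.

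**The case against.** The strongest reply is that this is a condensed article. Compression rules by ABI are the kind of detail a full protocol or site procedure holds, and the harmonized SOC protocols are not shown. The 40–60 mmHg figure follows a clause tying care to guidelines, and those guidelines may lower compression in PAD. The Discussion's remark can be read as describing how such patients are already treated. It also names no pressure, so it does not declare 60 mmHg unsafe for any given patient.

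Much of this stands. Whether the governing documents already contain a PAD rule cannot be settled from the article. The criterion used here, external pressure reaching ankle arterial pressure, is a reviewer's yardstick and not one the article states. The overlap rests on an assumed systolic pressure, and the figure applies to the decongestion phase only. Treatment is at specialist centers, where each visit includes "compression therapy documentation" and adverse event monitoring.

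It does not remove the point. The article does not merely omit detail: it prints a number, says care is standardized across sites, and elsewhere acknowledges a limit that the number does not reflect. A general reference to guidelines leaves the reader to decide which prevails.

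Three stronger readings are tempting and are not supported:
- *The target is unsafe for participants with PAD in general.* The working shows overlap only in a narrow corner of eligibility, and only at the upper part of the range.
- *The trial result is biased or underpowered.* Standard care is the same in both arms, and nothing in the sample size depends on this figure.
- *The maintenance stockings are also too strong.* The article gives no pressure for them and nothing has been calculated, so no claim is made.

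**Conclusion.** The point holds in a limited form and is minor. As printed, the decongestion target has no arterial condition. For participants who qualify by an ABI just above 0.5 and have a brachial systolic pressure below 120 mmHg, its upper end can meet or exceed ankle arterial pressure. The limits are an ABI of up to 0.60 at systolic 100 and up to 0.545 at systolic 110.

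How many participants this covers cannot be derived, because the article gives no distribution of ABI or blood pressure. The number may be very small, or zero. The conclusion rests on the assumed systolic values and on the printed text being what sites follow. If unseen SOC protocols already cap compression in PAD, what remains is a matter of stating it.

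**What to change.** Amend the Standard of care section along these lines:

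- In participants with PAD, the decongestion target is reduced and always stays below the ankle arterial pressure measured at screening. The sponsor's clinicians set the margin.
- Participants with preserved perfusion keep 40–60 mmHg.
- The same rule applies in both arms from the start of the run-in.

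If the full protocol or the harmonized SOC protocols already contain such a rule, restating it in this section is enough.

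**Cost.** One or two sentences. The ankle pressure is already obtained for eligibility, either directly or as part of the ABI. Sample size and the primary ANCOVA do not change. The Trial status section reports that recruitment began in October 2025, so this would be a change during the trial. If it is judged substantial, the protocol's own amendment provisions require notice to ethics committees, the registry and all investigators. The clinical downside is possibly slower healing in the few affected participants, under the same rule in both arms.
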